### Intravenous insulin infusion study 2:

Patients will be asked to return for a second insulin infusion study within one month of the first study. All procedures will be identical as described above, except that subjects having received glibenclamide during the first insulin infusion study will receive placebo capsules and vice versa.

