# Introduction:

Hypoglycemia is considered a limiting factor for insulin therapy in patients with diabetes mellitus type 1 and advanced diabetes type 2. Insulin-induced hypoglycemia not only causes symptomatic and sometimes temporarily disabling episodes but can be fatal. It also precludes the maintenance of euglycemia over a lifetime of diabetes and thus full realization of the benefits of glycemic control.

In healthy subjects the induction of hypoglycemia is followed by a coordinated hormonal response aimed at restoring normal blood glucose levels (1). Hypoglycemia results in suppression of endogenous insulin secretion from pancreatic β-cells and in increased secretion of counter regulatory hormones with glucagon and epinephrine being the first line response. All three of these physiologic defences may be defective in patients with type 1 diabetes rendering them at even increased risk for severe hypoglycemia (2). The lack of an adequate glucagon response to hypoglycemia occurs early in the course of type 1 DM and was first described by Gerich et al more than 30 years ago (3). In contrast to the defective epinephrine response, which is partially restored when hypoglycemic episodes are avoided, the impairment of the glucagon response is largely irreversible (4). The cessation of the adrenomedullary epinephrine response further promotes hypoglycemia-associated autonomic failure and hypoglycemia unawareness, thereby establishing a vicious cycle (2).

The most important stimulus for the pancreatic -cell to secrete glucagon in response to decreasing glucose concentrations has been found to be the resulting decrement in -cell insulin secretion. This has been concluded from studies demonstrating that both tonic stimulation of -cell insulin secretion by sulfonylureas and tonic inhibition of -cell insulin secretion by diazoxide impair the glucagon response to insulin induced hypoglycemia in healthy volunteers (5;6). According to this “insulin switch-off hypothesis” the impaired glucagon response during hypoglycemia in type 1 diabetes can be attributed to the intra-islet insulin deficiency and the resulting absence of a decrease in intra-islet insulin during hypoglycaemia (6).

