### Intravenous insulin infusion study 1:

Patients eligible to participate in the study protocol based on the results of the screening visit will be asked to discontinue or taper long-acting insulin at least 24 h before the intravenous insulin infusion study. Short acting insulin will be prescribed on an individual basis in order to keep capillary glucose concentrations between 5 and 11 mmol/l. All patients will be admitted to the Clinical Research Center, University Hospital Basel ([name], Klinikum 2, 6th floor) between 8 and 9 p.m. for approximately **22 hours**, including an overnight stay. They will be asked to remain fasted after their regular dinner between 6 and 7 p.m. on the day of admission until the end of the insulin infusion study. **Patients will be under close supervision of a study physician throughout their inpatient stay.**

Two intravenous catheters will be inserted in antecubital veins and after a baseline blood sample has been obtained, an intravenous infusion of regular human insulin (10 Units Actrapid HM® in 50 ml normal saline) in will be started and continued overnight by means of a syringe pump (Braun perfusor® compact S). Adjustments based on blood glucose measurements every 15 to 60 min will be made to maintain blood glucose concentrations between 5 -8 mmol/l until the beginning of the experiment the next morning. The blood glucose will be stabilized at 5 mmol/l one hour before the onset of the intravenous insulin infusion study (see below). The intravenous line will be kept patent by infusion of a small amount of isotonic (0.9%) saline.

*Application of study drugs:*

At 7.30 a.m. all patients will receive 15 mg glibenclamide (3 tablets Daonil® 5 mg, Sanofi-Aventis Schweiz AG, 1217 Meyrin, Switzerland) or 3 placebo capsules (Doralgan Tabletten, Institute of Pharmacy, University Hospital Basel, 4031 Basel, Switzerland) with 200 ml of tap water in a randomized order. Glibenclamide plasma concentrations can be expected to peak ~ 2 hours after oral ingestion (18). Thereby, peak plasma concentrations will coincide with the glucose nadir during the insulin infusion study (see below).

*Randomisation procedure:*

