A web-based random number generator ([www.random.org](http://www.random.org/)) will be used to assign a random number between 1 and 10 to each patient at the beginning of the first insulin infusion study. Those assigned an even number will receive glibenclamide during the first insulin infusion study and placebo pills during the second study. Patients assigned an odd number will receive the 2 therapies in reverse order.

*Insulin infusion and blood sampling:*

The intravenous insulin infusion test will be started at 8:30 a.m.. Regular human insulin will be infused at the rate of 30 mU/m²/min for 60 min and 15 mU/m²/min thereafter from 60 to 150 min in type 1 diabetics with a syringe pump (Braun perfusor® compact S) as previously described (19).. Venous blood samples will be taken at -30, -15, 0 min and at 5-10-min intervals over the next 150 min for the measurement of plasma glucose and at 15 min intervals for the measurement of plasma glucagon, epinephrine, metanephrine, growth hormone and cortisol concentrations. At the completion of the intravenous insulin study, the insulin infusion will be stopped, and 20% dextrose solution will be infused to re-establish normal glucose levels (4-8 mmol/l). The glucose infusion will be stopped when plasma glucose has stabilized >5 mmol/l for 30 min and a lunch will be served along with s.c. short acting insulin as needed. A total of 150 ml blood will be drawn during a metabolic stud

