***Restoration of s.c. insulin therapy and glucose monitoring***

**After completion of the insulin infusion study the patient’s glucose levels will be monitored every 30-60 minutes until 10 hours after the ingestion of the study drug. They will be discharged from the Clinical Research Center at 5:30 p.m.. The usual insulin regime will be resumed at a reduced dose for 24 hours (70% of the usual dose, see also below) to account for the potential increase in endogenous insulin secretion elicited by glibenclamide. If blood glucose values increase above 10 mmol/l using this approach, small dosages of short-acting insulin will be applied to decrease blood glucose levels to the desired range.**

*Assessment of hypoglycemia associated symptoms:*

To assess hypoglycemia associated symptoms, the Mood and Symptom Questionnaire (MSQ), the Complex Reaction Time Task (CRTT) and the Paced Auditory Serial Addition Task (PASAT) will be performed at baseline and every 30 minutes until restoration of euglycemic glucose levels (17;20;21).

The CRTT has been developed to measure sustained visual attention and psychomotor speed. During a 5 minute period participants have to respond to the presentation of coloured lights (which appear in random sequence) by pressing corresponding buttons as accurately and fast as possible. Using a PC based control algorithm the inter-stimulus intervals is shortened or lengthened, thereby modifying task difficulty so that subjects’ false response rate within a continuously moving window approaches 50 percent (20).

A computerized version of the PASAT will be employed as a measure of sustained and divided attention and executive function of the working memory. Pacing will be at 2.5 s intervals, total task duration will be 180 s. Subjects will be instructed to sum up the last to digits presented as fast and accurate as possible. Accuracy and verbal response time will be assessed. Several forms of the test will be used as to prevent simple learning effects (21).

*Safety measures:*

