The subjects’ consciousness during the insulin infusion study will be rated using the Glasgow coma scale (GCS) rating system every 5 min after plasma glucose has dropped below 3.5 mmol/l. If the grading decreases below 3 for best eye response (eye opening to speech), 3 for best verbal response (inappropriate words), 4 for best motor response (withdraws from pain) or plasma glucose concentrations decrease below 1.5 mmol/l, the insulin infusion will be stopped or tapered and small amounts of glucose (5-10g or 25-50 ml of a 20% dextrose infusion) will be given intravenously until the GCS rating and plasma glucose have increased above the previously mentioned limits.

Due to the prolonged duration of action of glibenclamide and its potential glucose lowering effects in type 1 diabetics with residual -cell function, patients will be instructed to taper their usual insulin dose **by 30 %** and monitor their capillary blood glucose every two to four hours and any time after the onset of symptoms suggestive of hypoglycemia for 24 hours after oral application of glibenclamide. They will be asked to ingest 10 grams of oral dextrose if capillary blood glucose concentrations drop below 4.0 mmol/l. When ever correction of blood glucose levels < 4.0 mmol/l becomes necessary, a repeat glucose measurement will be performed after one hour. All participants will be provided with the phone number of a study investigator in case any problems should arise after discharge from the clinical research center. **All patients will be advised to refrain from vigorous physical activity and driving motor vehicles within 24 hours after the ingestion of the study drugs**. **Furthermore, patients will be advised to increase the dosage of short acting insulin if blood glucose readings exceed 10 mmol/l.**

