## Potential risks and adverse events:

### Potential risks:

We consider the risks of this study to be mild. The specific risks are as follows:

Blood Loss: The total blood loss for this study will be approximately 300 ml.

Intravenous Catheters: Intravenous catheters used during the study are associated with a mild to moderate degree of pain upon insertion, and a small risk of localized infection.

Intravenous glucagon stimulation test: From our own experience the intravenous injection of glucagon is frequently associated with short-lasting (2-3 min) nausea and abdominal discomfort. Further side effects include vomiting, abdominal pain, paradoxic hypoglycemia, bradycardia (frequency 1:100 – 1:10’000) an rarely (frequency <1:10’000) with hypersensitivity, allergic reactions, hypoglycemic coma, tachycardia, hypotension, hypertension.

Intravenous insulin infusion: The intravenous insulin infusion is a safe technique which has been extensively used for the assessment of hypoglycemia counter regulation in type 1 diabetics (19). During the induction of hypoglycemia the subjects will be under close medical supervision. No long-term health effects can be anticipated from the induction of a short period of hypoglycemia. All infusions will be prepared under sterile conditions.

Insulin induced hypoglycemia following a bolus injection of regular human insulin (0.1-0.15 IU/kg body weight) is regularly used as a standard diagnostic procedure for the assessment of the hypothalamo-pituitary-adrenal axis and pituitary growth hormone secretory function at our institution. Venous plasma glucose concentrations between 1.5 and 2.0 mmol/l are regularly achieved during this procedure. Based on previous studies, the glucose nadir during our study can be anticipated to be around 2.0 mmol/l (40 mg/dl) (19). The insulin infusion will be discontinued or tapered if the plasma glucose concentration decreases below the threshold of 1.5 mmol/l (30 mg/dl) or significant impairment of consciousness occurs at any time point of the experiment (see section 3.3.3 – safety measures).

To minimize the potential risks associated with profound hypoglycemia, patients with a history of epilepsy, seizures and coronary disease are not eligible to participate. The upper age limit of 50 years and the exclusion of current smokers and patients with inadequate glycemic control (HbA1c > 8%) further minimizes the risk of silent coronary disease which may become clinically apparent during hypoglycemia.

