Glibenclamide: Glibenclamide is a widely used drug for the treatment of type 2 diabetes. Possible adverse effects are headache, diarrhoea, constipation, nausea, vomiting or abdominal pain, allergic reactions such as skin rashes. Hypoglycemia due to the stimulation of -cell insulin secretion is the most common side effect. Since -cell function is severely impaired in type 1 diabetes, we do not expect significant insulin release following oral glibenclamide in the patients included in the study. Therefore, the risk of hypoglycemia will be minimal. Nevertheless, patients will be instructed to closely monitor their blood glucose levels and reduce their usual insulin dose by **30%** for up to 24 hours after glibenclamide treatment.

Placebo pills: No adverse effects can be anticipated from the intake of placebo pills.

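### The cross-over caps the gap between the two induced-hypoglycaemia studies at one month but sets no minimum, so study 2 could follow study 1 by about 3 days

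*Protocol*

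**What the plan says.** The section Intravenous insulin infusion study 2 gives the only rule on spacing: "Patients will be asked to return for a second insulin infusion study within one month of the first study". No section gives a minimum interval or a wash-out.

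Two other rules delay study 2 in practice:

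- After study 1 (Restoration of s.c. insulin therapy and glucose monitoring): "The usual insulin regime will be resumed at a reduced dose for 24 hours", following discharge at 5:30 p.m.
- Before each study (Intravenous insulin infusion study 1), patients are asked to "discontinue or taper long-acting insulin at least 24 h before the intravenous insulin infusion study". They are admitted between 8 and 9 p.m. on the evening before.

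Four statements bear on why the gap matters:

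- The Introduction says of the defective epinephrine response: "which is partially restored when hypoglycemic episodes are avoided, the impairment of the glucagon response is largely irreversible".
- Potential risks says that "the glucose nadir during our study can be anticipated to be around 2.0 mmol/l".
- Safety measures justifies its 24 h precautions with these words: "Due to the prolonged duration of action of glibenclamide and its potential glucose lowering effects in type 1 diabetics" (the sentence goes on to restrict this to patients with residual β-cell function).
- On the drug itself, Potential risks concludes: "Therefore, the risk of hypoglycemia will be minimal".

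The order of treatments is set by an even or odd random number: "Those assigned an even number will receive glibenclamide during the first insulin infusion study and placebo pills during the second study". Odd numbers get the reverse order.

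**The concern.** A cross-over compares each patient with himself or herself, so the second period should not carry traces of the first. Here the first period leaves two possible traces: a recent deep hypoglycaemia in every patient, and residual drug in those who took glibenclamide first. The spacing rule fixes the side of the interval that does not protect the comparison and leaves the other side open.

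The outcomes exposed are not the same for both traces. The Introduction names glucagon and epinephrine as the first-line defences and ties partial recovery of the epinephrine response to avoiding hypoglycaemia. A short gap could therefore affect epinephrine, the symptom scores repeated in each study, and glucose recovery from 60 to 150 min, which is the first secondary endpoint in Data analysis. The primary endpoint, glucagon AUC from 0 to 150 min, is less exposed, because the Introduction regards the loss of that response as mostly permanent. It remains open to drug carry-over. It also remains open in C-peptide-positive patients, the comparator group in Study objectives, if they still have a glucagon response that can change.

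**Working it through.** **Shortest compliant gap.** All times come from Intravenous insulin infusion study 1 and from the restoration section. Day 0 is the day of study 1: tablets at 7:30 a.m., infusion from 8:30 a.m., discharge at 5:30 p.m.

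- *The two 24 h rules run one after the other.* Reduced insulin lasts until 5:30 p.m. on day 1. Stopping or tapering long-acting insulin then takes until 5:30 p.m. on day 2. Admission is at 8–9 p.m. on day 2, with tablets at 7:30 a.m. on day 3. The gap is 3 × 24 = 72 h.
- *The two rules overlap.* The taper takes place during day 1, with admission at 8–9 p.m. on day 1 and tablets at 7:30 a.m. on day 2. The gap is 2 × 24 = 48 h. The result is the same if both 24 h periods run in sequence but the first is counted from tablet intake, as Safety measures does.

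The stated maximum is one month, that is day 30 or 31. The rule therefore allows any gap from day 2 or 3 to day 30 or 31.

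**Residual glibenclamide at the second dose.** The protocol gives no half-life, so 5, 10 and 20 h are assumptions chosen to show a range. Fraction remaining = 2^(−gap / half-life).

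| Gap | 5 h | 10 h | 20 h |
|---|---|---|---|
| 48 h | 2^−9.6 = 0.13% | 2^−4.8 = 3.6% | 2^−2.4 = 18.9% |
| 72 h | 2^−14.4 = 0.005% | 2^−7.2 = 0.7% | 2^−3.6 = 8.2% |
| 168 h (7 days) | about 0% | 2^−16.8 = 0.0009% | 2^−8.4 = 0.30% |

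**What this would do to the drug contrast.** Only the placebo period of the glibenclamide-first order is affected. Suppose that half the patients have that order and that the effect is proportional to the residual fraction. The average treatment difference then shrinks by half the fraction:

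- At 48 h: 3.6% / 2 = 1.8% (10 h) or 18.9% / 2 = about 9.5% (20 h).
- At 72 h: 0.7% / 2 = about 0.3% (10 h) or 8.2% / 2 = 4.1% (20 h).
- At 7 days: at most 0.30% / 2 = 0.15%.

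The shift is towards no difference.

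**After-effect of the first hypoglycaemia.** No arithmetic is possible. The document gives neither its size nor its duration.

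**The case against.** The strongest reply is that no harm is shown. The Introduction speaks of an already defective epinephrine response that improves when episodes are avoided. It does not say that one supervised episode weakens the response days later, by how much, or for how long. Drug carry-over is small unless the half-life is long. The protocol also has short-term safeguards: monitoring until 10 h after the tablets, a 30% insulin reduction with glucose checks for 24 h, and overnight glucose held at 5–8 mmol/l before each study. Investigators may well schedule longer gaps anyway.

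Most of this stands, and it limits how strongly the point can be put. It does not remove the point. The safeguards limit new hypoglycaemia but put no time between the two induced episodes. The interval between periods is a visit-schedule rule, and a statistical analysis plan cannot restore a gap that was not kept.

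Some stronger readings are tempting but unsupported:

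- *The primary result is biased.* The document's own view of the glucagon defect points to little exposure beyond the two routes named above.
- *The hypoglycaemia after-effect biases the treatment comparison.* Study 1 induces hypoglycaemia under both treatments. An after-effect that is equal in both orders is a period effect, which balanced orders or a period term can remove. Whether chance makes the orders unequal is a question about the allocation method and does not depend on the gap.
- *The protocol breaks its own four-week rule.* That rule, in Study population, is an entry criterion about severe episodes. Nothing extends it to the hypoglycaemia induced in study 1.
- *Hypoglycaemia awareness is affected.* The awareness questionnaire is given at the screening visit, before study 1. Only the symptom questionnaire and the cognitive tests are repeated during the infusion studies.

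**Conclusion.** The gap in the rule is real: an upper limit, no lower limit, and a shortest compliant interval of about 3 days, or 2 days where the insulin rules overlap. The possible effect falls mainly on glucose recovery, epinephrine and repeated symptom scores. For the primary glucagon AUC it comes mainly through drug carry-over or in C-peptide-positive patients. The carry-over part rests on assumed half-lives of 5 to 20 h and on an effect proportional to residual drug. On that basis it dilutes the contrast by at most about 9.5% at 48 h and 4.1% at 72 h, and by much less at shorter half-lives. The hypoglycaemia part cannot be sized from the document. This is a cheap improvement and does not show that the trial's main conclusion would be wrong.

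**What to change.** In Intravenous insulin infusion study 2, replace the timing rule with: the second study takes place at least 7 days and at most one month after the first.

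On the assumed half-lives, this leaves at most 0.3% of the drug and rules out repeats after 2 or 3 days. It should not be presented as a proven wash-out for the hypoglycaemia after-effect, because the document gives no duration for that. If the investigators have such a figure, they should set the minimum from it.

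Cost: scheduling days 2 or 3 to 6 are lost, that is 5 or 4 days. Days 7 to 30 or 31 remain, which is 24 or 25 days. No visit, procedure or blood draw is added, and the one-month maximum is unchanged.

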## Study medication:

Glibenclamide 5 mg tablets (Daonil® 5 mg, Swissmedic No. 35402, Lot-No. 40E108, expiration date 06.2008) has been purchased from Sanofi Aventis Schweiz AG, 1217 Meyrin, Switzerland.

Placebo tablets (Doralgan capsules, Lot-No. 060825N01, expiration date 08.2008) has been purchased from the Institute of Pharmacy at the University Hospital Basel, 4031 Basel, Switzerland.

Insulin Actrapid (Actrapid HM®, Swissmedic No. 44610, Lot-No. SW50921, expiration date 08.2008) has been purchased from Novo Nordisk Pharma AG, 8700 Küsnacht, Switzerland.

Glucagon 1 mg (GlucaGen Novo Nordisk® 1 mg ampules, Swissmedic No. 31489, Lot-No. SW60346, expiration date 01.2009) has been purchased from Novo Nordisk Pharma AG, 8700 Küsnacht, Switzerland.

## Potential risks and adverse events:

### Potential risks:

We consider the risks of this study to be mild. The specific risks are as follows:

Blood Loss: The total blood loss for this study will be approximately 300 ml.

Intravenous Catheters: Intravenous catheters used during the study are associated with a mild to moderate degree of pain upon insertion, and a small risk of localized infection.

Intravenous glucagon stimulation test: From our own experience the intravenous injection of glucagon is frequently associated with short-lasting (2-3 min) nausea and abdominal discomfort. Further side effects include vomiting, abdominal pain, paradoxic hypoglycemia, bradycardia (frequency 1:100 – 1:10’000) an rarely (frequency <1:10’000) with hypersensitivity, allergic reactions, hypoglycemic coma, tachycardia, hypotension, hypertension.

Intravenous insulin infusion: The intravenous insulin infusion is a safe technique which has been extensively used for the assessment of hypoglycemia counter regulation in type 1 diabetics (19). During the induction of hypoglycemia the subjects will be under close medical supervision. No long-term health effects can be anticipated from the induction of a short period of hypoglycemia. All infusions will be prepared under sterile conditions.

Insulin induced hypoglycemia following a bolus injection of regular human insulin (0.1-0.15 IU/kg body weight) is regularly used as a standard diagnostic procedure for the assessment of the hypothalamo-pituitary-adrenal axis and pituitary growth hormone secretory function at our institution. Venous plasma glucose concentrations between 1.5 and 2.0 mmol/l are regularly achieved during this procedure. Based on previous studies, the glucose nadir during our study can be anticipated to be around 2.0 mmol/l (40 mg/dl) (19). The insulin infusion will be discontinued or tapered if the plasma glucose concentration decreases below the threshold of 1.5 mmol/l (30 mg/dl) or significant impairment of consciousness occurs at any time point of the experiment (see section 3.3.3 – safety measures).

To minimize the potential risks associated with profound hypoglycemia, patients with a history of epilepsy, seizures and coronary disease are not eligible to participate. The upper age limit of 50 years and the exclusion of current smokers and patients with inadequate glycemic control (HbA1c > 8%) further minimizes the risk of silent coronary disease which may become clinically apparent during hypoglycemia.

Glibenclamide: Glibenclamide is a widely used drug for the treatment of type 2 diabetes. Possible adverse effects are headache, diarrhoea, constipation, nausea, vomiting or abdominal pain, allergic reactions such as skin rashes. Hypoglycemia due to the stimulation of -cell insulin secretion is the most common side effect. Since -cell function is severely impaired in type 1 diabetes, we do not expect significant insulin release following oral glibenclamide in the patients included in the study. Therefore, the risk of hypoglycemia will be minimal. Nevertheless, patients will be instructed to closely monitor their blood glucose levels and reduce their usual insulin dose by **30%** for up to 24 hours after glibenclamide treatment.

Placebo pills: No adverse effects can be anticipated from the intake of placebo pills.

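### The glucose limit for stopping or tapering the insulin infusion is printed as two unequal values: 1.5 mmol/l is 27 mg/dl, not 30

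*Protocol*

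**What the plan says.** The rule for interrupting the insulin infusion appears twice in the Protocol.

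- **Potential risks, paragraph on the intravenous insulin infusion.** The infusion is stopped or tapered if plasma glucose "decreases below the threshold of 1.5 mmol/l (30 mg/dl) or significant impairment of consciousness occurs at any time point of the experiment". The sentence then points the reader elsewhere: "see section 3.3.3 – safety measures". Just before it, the paragraph states what is expected: "the glucose nadir during our study can be anticipated to be around 2.0 mmol/l (40 mg/dl".
- **Safety measures, under Intravenous insulin infusion study 1.** This is the operational text. On glucose it says that if "plasma glucose concentrations decrease below 1.5 mmol/l, the insulin infusion will be stopped or tapered", and it adds small amounts of intravenous glucose. It gives no mg/dl figure. On consciousness it uses separate coma-scale limits for eye, verbal and motor response ("If the grading decreases below 3 for best eye response (eye opening to speech), 3 for best verbal response (inappropriate words" and "4 for best motor response (withdraws from pain"). The scale is rated "every 5 min after plasma glucose has dropped below 3.5 mmol/l".

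**The concern.** A threshold printed in two units has to be the same threshold in both. Here it is not, and it is the limit that ends or reduces a deliberately induced hypoglycaemia. The experiment is also expected to run close to it: by the Protocol's own figures the nadir lies only 0.5 mmol/l above the mmol/l limit. Anyone who worked from the mg/dl figure would act at a higher glucose than someone who worked from the mmol/l figure.

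The consciousness criterion raises a smaller question. The Potential risks section applies it throughout the experiment, whereas the Safety measures text starts the ratings only once glucose has fallen to a stated level.

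**Working it through.** **Inputs**

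- Stop threshold: 1.5 mmol/l and 30 mg/dl (Potential risks); 1.5 mmol/l only (Safety measures).
- Expected nadir: 2.0 mmol/l and 40 mg/dl (Potential risks).
- Molar mass of glucose: 180.16 g/mol. The Protocol does not give it; it is a physical constant and the only outside figure used.

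**Formula:** mg/dl = mmol/l × 180.16 / 10 = mmol/l × 18.016.

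**Attempt to reproduce the printed figures.** The usual factors do not give 30 or 40:

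| Factor | 1.5 mmol/l | 2.0 mmol/l |
|---|---|---|
| 18 | 27.0 | 36.0 |
| 18.016 | 27.02 | 36.03 |
| 18.02 | 27.03 | 36.04 |
| 20 | 30 | 40 |

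Only a factor of 20, or rounding the correct result to the nearest 10 mg/dl, yields both printed values. Rounding to the nearest 5 would give 25 and 35.

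**Size of the error**

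- Threshold: 30 / 27.02 = 1.11, so the printed mg/dl figure is 11% too high for its mmol/l partner.
- Nadir: 40 / 36.03 = 1.11, also 11% too high.
- In reverse: 30 / 18.016 = 1.67 mmol/l, and 40 / 18.016 = 2.22 mmol/l.

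**Band in which the two limits disagree**

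- A reading from 1.50 to just under 1.67 mmol/l (27 to just under 30 mg/dl) is not below the mmol/l limit but is below the mg/dl limit.
- Width: 1.67 − 1.50 = 0.17 mmol/l.
- Distance from expected nadir to limit, both in mmol/l as printed: 2.0 − 1.5 = 0.5 mmol/l.
- Ratio: 0.17 / 0.5 = 0.34 from the rounded figures, 0.33 unrounded (0.165 / 0.5). That is about a third.

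**Consciousness criterion, side by side**

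| | Potential risks | Safety measures |
|---|---|---|
| When it applies | any time in the experiment | ratings every 5 min once plasma glucose is below 3.5 mmol/l |
| What triggers action | significant impairment, no score given; refers to the safety measures | eye below 3, verbal below 3, or motor below 4 |

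The first row shows a difference in scope. Glucose is to be stabilised at 5 mmol/l before the test, so no coma-scale rating is scheduled between the start of the infusion and the fall below 3.5 mmol/l. The second row shows a summary and the definition it refers to.

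**The case against.** The strongest reply is that the mg/dl figures govern nothing. They occur only twice in the Protocol, both times in parentheses in the risk narrative. Every other glucose limit is in mmol/l, and the operational rule under Safety measures states 1.5 mmol/l without a conversion. The mmol/l value is identical in both places, the study runs at one site, and nothing suggests that its staff work in mg/dl. Both pairs look like rounding to the nearest 10, and the nadir is only approximate and triggers no action. Nearly all of this stands, and it limits the practical weight of the point. It does not make the two printed values equal. Coarse rounding is harmless for a descriptive nadir but not for a decision limit.

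A reader might go further in two directions that the document does not support.

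- **That the two sections contradict each other on consciousness, with the coma-scale limits set far below what the risk section promises.** The risk section gives no score. It refers in the same sentence to the safety measures, and by the order of headings section 3.3.3 is the one that contains them. In that sentence the word *any* qualifies the time point, not the degree of impairment. To call the coma-scale limits too low, a reader would have to supply a personal threshold for what is significant, which is a clinical judgement. Adding the three limits (3 + 3 + 4 = 10) does not help either: the rule uses no total, and one component below its own limit is enough to trigger action.
- **That the mismatch distorts the glucagon area under the curve (0 to 150 min) or the glucose recovery rate (60 to 150 min).** Stopping insulin and giving glucose would plainly change both in a patient to whom it happened. But the Protocol gives no basis for how many patients would have readings in the 0.17 mmol/l band, or for anyone acting on the mg/dl figure. The choice between stopping and tapering is in any case left open in both sections. No effect on the endpoints is shown.

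**Conclusion.** The arithmetic error is certain and rests only on the molar mass of glucose. The stop threshold carries two values, 1.5 mmol/l and 30 mg/dl (1.67 mmol/l), which differ by 0.17 mmol/l, or 11%. The expected nadir has the same proportional error.

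The practical effect is probably small, on the assumption that staff follow the Safety measures text and read glucose in mmol/l. The point has no bearing on sample size, power or type I error. It still deserves correction, because a safety decision limit should have one value and the change costs almost nothing.

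The consciousness wording is a clarity point about when the criterion is assessed, not a contradiction about the level at which it is met. Which glucose limit is clinically right is not judged here.

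**What to change.** - Reconcile the glucose stop threshold in Potential risks with that in Safety measures, so that a single value appears in both, either in one unit only or with a correct conversion. The responsible clinicians should confirm which limit is meant.
- Correct the conversion of the expected nadir in the same paragraph, or drop the mg/dl figure.
- Align the wording on when consciousness is assessed, so that the two sections describe the same scope. The clinicians decide what that scope is.

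The cost is a wording change to the Protocol. Design, sample size and analysis are unaffected.
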